#### **2.4.7.2 Compliance**

Compliance with the programme will be assessed by providing to the coaches with additional forms to record the details of each time the “11+” will be used as the warm up into the team as well as the number of players who performed them (Appendix N). Completeness of the forms will be reviewed regularly by the research team.

#### **2.4.7.3 Data management**

The hard copies of the forms from the coaches and the medical personnel will be kept in a locked and secure drawer in the researchers’ office after being scanned to keep the soft copies of the collected data. The electronic copies will then be saved on a password protected computer and external hard drive for back up.

#### **2.4.8 Statistical analysis**

Analysis of the incidence of injuries comparing the two study groups and the two divisions will be done as explained in the study one. Demographic characteristics of the coaches and responses on the knowledge, perception, readiness and decision making assessment will be analysed using descriptive statistics (range, mean, standard deviation). Categorical data like the coaches’ level of education, highest level of coaching license, availability of the medical personnel into the team will be presented as frequency and percentages. The five injury prevention readiness to practice questions will be coded from zero to five. The minimum score will be zero and the maximum score will be 25. The responses from the perception questions that are on a 5-point Likert scale will be recorded on a range from 1=“very unlikely” to 5=“very likely”. Therefore the results will be analysed using the descriptive statistics with means and standard deviation. Pearson correlation will be used to assess the relationship between perception variable and coaches’ readiness of sports injury prevention. The same test will be used to assess the association between readiness, perception, and first aid knowledge and compliance with the injury prevention programme. Analysis of variance test (ANOVA) will be used to analyse the difference between the coaches’ perceptions, knowledge, and readiness regarding injury prevention in the first division and the second division. The level of significance for all the tests

is set to 0.05. The details of all the statistical analysis that will be performed are provided in the appendix J.

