### **2.3.9 Statistical analysis**

All data will be analyzed statistically using STATISTICA version 12. Standard descriptive statistics will be used for numerical variables as means, standard deviations (SD) or 95% confidence intervals (CI).

In this study incidence for all injuries will be expressed as injuries per 1000 soccer playing hours for the purpose of the comparison with previous epidemiological studies. Risk per 1000 hours of exposure either per match, training or both will be equal to number of injuries multiplied by 1000 per total exposure time. The variations of injuries during match, training or both for the two seasons will be analyzed using Analysis of Variance (ANOVA). ANOVA will also be used to analyze the occurrence of injuries according to the position in the team and division of play. The categorical variables such as the frequency, type, location, severity as well as the mechanism of injuries will be analyzed using a Chi-square test or Fisher's exact test for small numbers. Between groups incidence of injuries will be compared using z-statistics and rate ratios (RR) with a 95% CI will used to present data. The level of significance for all the tests is set to 0.05. Univariate and multivariate regression analyses will be used to calculate odds ratios (ORs) and 95% confidence intervals (CIs) for  $\pm 1$  standard deviation of change. The details of all the statistical analysis that will be performed are provided in the appendix J.

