#### **2.4.1.1 Objectives**

- a. To assess if there is an increase in the knowledge of coaches towards injury prevention before and after the intervention
- b. To assess if there is any difference in perception of the soccer coaches towards injury prevention before and after intervention
- c. To assess whether the introduction of an injury prevention programme will increase the readiness for injury prevention practice of soccer coaches

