Coaches will also be trained on first aid. During the training, they will receive the first aid course for two days that will be provided by the trainer from the Rwanda Red Cross. Questionnaires will be distributed to the coaches to assess their knowledge immediately after first aid training. At the end of season two (June 2016) questionnaires will be distributed to the coaches from both divisions to assess the knowledge retained after one year of intervention.

Coaches and medical personnel from the first division will be requested to continue the recording of injuries and exposure using the procedure they used in the season one (2014-2015). To increase compliance and proper recording, coaches will be visited at team practice by the researcher to see if proper implementation is occurring and additional instructions on the correct conduct of the exercises will be provided where necessary. Data collection during season two (2015-2016) will be the same as season one where players exposure time, occurrence of injuries, treatment will be assessed.

Figure 3: Study two framework

[figure not shown]

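### Section 2.4.8 correlates coaches' perception with readiness without saying which coaches or questionnaire round enter, and names no adjustment for division or trial arm

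*Combined protocol and SAP*

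**What the plan says.** **The test.** Section 2.4.8: "Pearson correlation will be used to assess the relationship between perception variable and" coaches' readiness. It continues: "The same test will be used to assess the association between readiness, perception, and first aid knowledge and compliance with the injury prevention programme". No covariate or stratum is named. The section does not say whether first-division coaches, second-division coaches, one trial arm or everyone enters, or at which questionnaire round. Section 2.3.9 states "The level of significance for all the tests is set to 0.05", and 2.4.8 repeats that level.

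**Division.** Section 2.4.8 also plans an ANOVA of perceptions, knowledge and "readiness regarding injury prevention in the first division and the second division". Section 2.4.4 gives a reason why divisions might differ: first-division coaches deal less with injuries because their clubs have medical staff.

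**Training.** Objective b in 2.4.1.1 reads "To assess if there is any difference in perception of the soccer coaches towards injury prevention before and after intervention". Objective c asks whether the programme "will increase the readiness for injury prevention practice of soccer coaches". Section 2.4.6 invites only the second-division intervention arm to the training.

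**Rounds.** Section 2.4.7.1 describes questionnaires in preseason, again in the preseason after season one, immediately after the first-aid training, and in June 2016. At that last round "questionnaires will be distributed to the coaches from both divisions", with retained knowledge as the stated purpose.

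**Details.** Section 2.4.8 refers to Appendix J for the full analysis. That appendix is not in the supplied text.

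**The concern.** The coaches who may answer the questionnaire fall into three groups: first division, trained second division and untrained second division. A Pearson correlation over a mixture of groups combines two things: the relation between the scales among comparable coaches, and the differences between group means. If one group scores higher on both scales, the pooled coefficient is positive even when the scales are unrelated inside every group. If group means move in opposite directions, a real relation can be hidden.

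What is at stake is interpretation. A significant coefficient would naturally be read as saying that coaches who perceive more risk or benefit are readier to act, which would support working on perceptions. A pooled coefficient cannot separate that from the statement that trained coaches, or coaches of one division, score higher on both scales.

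**Working it through.** **Inputs from the documents.** 14 first-division and 19 second-division clubs (2.1); at least one head coach per second-division team (2.4.4); arms of nine and ten teams (2.4.4.4); significance level 0.05 (2.3.9, 2.4.8).

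**Assumptions.** One head coach per first-division club; alternatively two coaches per team in both divisions, treated as independent; ten teams in the trained arm; a two-sided test; normal scores; zero correlation inside each group; the same shift *d* (in within-group SDs) on both scales. The documents give no value for *d*, so I used 0.5, 0.8 and 1. For the training rows I followed 2.4.6, where only the intervention arm is trained. Section 2.2 speaks of first-aid training for control-group coaches, and the two sections need to be reconciled.

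**Pooled correlation.** Let *p* be the share of coaches in the shifted group and *q* = 1 − *p*. With no within-group relation,

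r = pq·d₁d₂ / √[(1 + pq·d₁²)(1 + pq·d₂²)].

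For 14 versus 19 coaches, pq = (14/33)(19/33) = 0.244. With equal shifts:
- d = 0.5: 0.061/1.061 = 0.058
- d = 0.8: 0.156/1.156 = 0.135
- d = 1: 0.244/1.244 = 0.196

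For 10 trained among 33 coaches, pq = (10/33)(23/33) = 0.211, so at d = 1, r = 0.211/1.211 = 0.174.

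**The plan's own figure first.** With no group difference, the plain test (t = r√(n−2)/√(1−r²), n−2 degrees of freedom) is significant in 4.9% of simulated data sets, both for 14 versus 19 and for 10 versus 9. That is the nominal 5% within simulation error.

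**With group shifts on both scales** (100,000 simulated data sets per cell), share of data sets in which the plain test is significant:

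| Groups pooled | Sizes | 0.5 SD | 0.8 SD | 1 SD |
|---|---|---|---|---|
| Two divisions, one coach per team | 14 / 19 | 6.2% | 11.8% | 19.8% |
| Two divisions, two per team | 28 / 38 | 7.3% | 19.4% | 35.8% |
| Two arms, second division only | 10 / 9 | 5.6% | 8.6% | 13.3% |
| Two arms, two per team | 20 / 18 | 6.5% | 13.1% | 22.9% |
| All coaches, trained arm shifted | 14 / 10 / 9 | 6.0% | 10.1% | 16.5% |
| All coaches, two per team, trained arm shifted | 28 / 20 / 18 | 6.7% | 15.9% | 29.6% |

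Centring both scales on their group means (a partial correlation given group) gives 4.8% to 5.2% in every cell.

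**Limits on the inflation.**
- If only one scale shifts, by 1 SD, the rate stays at about 5% (5.3% for 14 versus 19).
- If training moves readiness by 1 SD but perception by only 0.3 SD, it is about 6% to 7%.
- At 0.3 SD on both scales it is 5.0% to 5.4%.

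**The opposite error.** With a within-group correlation of 0.5 and division shifts of +1 and −1 SD (14 versus 19), the pooled test is significant in 18% of data sets, against 85% for the adjusted one.

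**The case against.** **Pooling is not stated.** Study two's participants are second-division coaches (2.4.4, 2.4.4.1), and the June 2016 round in both divisions is described as a check on retained knowledge. A correlation in the second division before training would carry neither a division nor a training effect. This stands. What the text shows is that the population and round are unspecified, not that groups will be pooled.

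**The plan does not predict differences.** A reader might infer that the plan expects both scales to differ by division and to change with training. It does not say so. The ANOVA is neutral, the perception objective asks for any difference, and only the readiness objective has a direction.

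**The 5% level is not broken for the literal question.** A reader might also infer that the test has an inflated false-positive rate. The plan asks for the relationship between perception and readiness with no condition of comparable coaches. If groups differ on both scales, that overall correlation is truly non-zero and rejecting is not an error. The percentages above are error rates only for the within-group question. That is the question needed for the natural interpretation, but it is not the one written down.

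**Moderate shifts do little.** This stands too: both scales must shift, and at 0.5 SD the excess over 5% is at most about 2.5 points.

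**Low consequence.** No objective in 2.4.1.1 or 2.4.2.1 asks for this correlation. The correlations with compliance are also less exposed to mixing of arms, since compliance means use of the 11+, which only the intervention arm is taught.

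**Appendix J** may settle the population, round or adjustment, and could not be checked.

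**Conclusion.** The point holds in a limited form. As written, 2.4.8 leaves open who and which round enter the perception–readiness correlation, and names no adjustment for two factors that the plan itself examines as sources of difference in both scales. If groups are pooled and both scales shift together, a significant coefficient may only restate group differences.

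The size depends wholly on assumed shifts. It is negligible to small up to 0.5 SD and becomes material from about 0.8 to 1 SD, more so with two coaches per team. With no group differences the plain test is correct. This is a minor improvement to a supporting analysis. The before-and-after comparisons of coaches and the injury-incidence results do not depend on it.

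**What to change.** In 2.4.8:

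1. State which coaches enter the correlation and at which questionnaire round. Make the preseason 2015 round, completed before training, the main analysis. Define it as before training rather than by month, because 2.4.6 and 2.4.7.1 give different months for the training and must be reconciled.
2. Replace the plain Pearson test by a partial correlation, or a linear regression of readiness on perception, adjusted for division where both divisions enter and also for trial arm in any post-training round.
3. If several coaches per team or repeated rounds are used, allow for that dependence.
4. Align Appendix J with this text.

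The cost is one or two degrees of freedom and a few sentences, with no new data. Little power is lost if the groups do not differ: with a true correlation of 0.5 and 33 coaches, the plain test is significant in 86% of simulated data sets and the adjusted one in 85%.

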#### **2.4.3 Study design**

A cluster-randomized controlled trial will be used in this study with teams as units of randomization.

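### Aim 1 of Study Two (coaches' knowledge, perception and readiness) has no stated analysis that uses the randomisation

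*Combined protocol and SAP*

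**What the plan says.** Section 2.4.3 sets the design: "A cluster-randomized controlled trial will be used in this study with teams as units of randomization". Aim 1 concerns the coaches. Its objectives in 2.4.1.1 are framed over time: "To assess if there is an increase in the knowledge of coaches towards injury prevention before and after the intervention" and "To assess if there is any difference in perception of the soccer coaches towards injury prevention before and after intervention". The third objective asks whether readiness rises once the programme is introduced. None of the three mentions the control group.

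Section 2.4.8 compares the randomised groups for one outcome only: "Analysis of the incidence of injuries comparing the two study groups and the two divisions will be done as explained in the study one". For coach scores it gives descriptive statistics, correlations ("Pearson correlation will be used to assess the relationship between perception variable" and readiness, and with compliance) and one group test, an ANOVA of coaches' "perceptions, knowledge, and readiness regarding injury prevention in the first division and the second division". That sentence names no time point. No paired test, repeated-measures test or arm comparison is named for these scores. The section refers to Appendix J for details.

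On timing, 2.4.7.1 gives questionnaires to coaches in an undated preseason and again before 2015-2016, without restriction to one arm. After the training it says: "Questionnaires will be distributed to the coaches to assess their knowledge immediately after first aid training". In June 2016, "questionnaires will be distributed to the coaches from both divisions to assess the knowledge retained after one year of intervention".

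**The concern.** A trial that randomises teams and then trains the coaches of one arm has a natural test of the training: compare the arms. The text does not state that test for Aim 1.

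The before-after change in the objectives has no control. Coaches who stay in post meet the questionnaire repeatedly, 2.4.4 describes other coach training by FIFA and CAF, and 2.4.7.1 expects coaches to change between seasons. Any of these could look like a training effect.

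The division ANOVA compares groups that were not randomised and that 2.4.4 itself describes as different in medical support, staffing and the coach's part in handling injuries. At stake is whether one of Study Two's two aims can support a causal conclusion. With no contrast and time point fixed in advance, there is also room to choose among several after the data are seen.

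**Working it through.** The plan gives no sample size, SD or expected effect for coach scores, so there is no figure to reproduce. The check asks what each stated contrast would estimate.

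**Inputs**
- 19 second-division teams, in groups of nine and ten (2.4.4.4); 14 first-division teams (2.1).
- At least one head coach per team (2.4.4). One per team is assumed below.
- Significance level 0.05 (2.4.8). Two-sided is assumed.
- Training offered to intervention-arm coaches (2.4.6, 2.4.7.1). Sections 2.2 and 2.4.4 conflict with this; see step 4.

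**1. Who answers when (2.4.7.1)**
- First preseason (undated) and preseason 2015: coaches, not limited to one arm.
- Immediately after first aid training: by its timing, trained coaches only.
- June 2016: both divisions, so control-arm coaches are included.

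A trained coach in post throughout answers up to four times, and a control coach up to three. Baseline and final occasions therefore exist in both arms, but the immediate post-test has no control counterpart.

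**2. What each contrast estimates**

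Let D be the training effect, R the change that would have occurred anyway, B the existing difference between divisions, and k the number of trained second-division teams. Take R as equal in all groups.
- Before-after in trained coaches: D + R.
- Second minus first division, before training: B.
- Second minus first division, after training: B + (k/19) × D, with equal coach numbers per team.
- Arm comparison within the second division: (D + R) − R = D.

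Only the last isolates D. Randomisation makes R equal in expectation between arms. One residue remains: the extra questionnaire given to trained coaches becomes part of what is compared.

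**3. Size of the dilution, if the division contrast is read as a training effect**
- k = 9: 9/19 = 0.474. k = 10: 10/19 = 0.526.
- For an assumed D of 1.0 SD and B = 0, the division contrast shows 0.47 to 0.53 SD. Two-sample t-test power with 14 versus 19 coaches is about 26% to 30%.
- For the same D, the arm contrast with 9 versus 10 coaches has about 54% power.

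**4. Dependence on who is trained**
- Sections 2.4.6 and 2.4.7.1 invite intervention-arm coaches only.
- Section 2.4.4 puts the minimum number of coaches trained at 19, which is one for every second-division team. Then k/19 = 19/19 = 1, there is no dilution, and no untrained arm is left.
- Section 2.2 gives control-group coaches additional training in first aid and injury treatment. First aid knowledge is measured in Section D of the questionnaire (2.4.5.1), so on that reading an arm contrast on that section is not trained versus untrained.

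**5. Precision of the arm contrast (9 versus 10 coaches, unadjusted)**
- Normal approximation at 80% power: (1.960 + 0.842) × √(1/9 + 1/10) = 2.802 × 0.4595 = 1.29 SD.
- Exact t-test: about 1.37 SD at 80% power and 1.58 SD at 90%.
- Power for assumed true effects of 0.8, 1.0 and 1.5 SD: about 38%, 54% and 87%.

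Baseline adjustment, or including assistant and goalkeeper coaches, would change these figures.

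**The case against.** Five arguments can be made for the plan.

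- **Appendix J.** It is listed as a data analysis table and both statistical sections defer to it, but it was not in the text available. It may name an arm comparison or a paired test. This stands, and it limits the point to 2.4.8 and the objectives. A reader might infer that the control coaches' scores go unused; the documents do not establish that.
- **The role of the ANOVA.** A reader might infer that the plan chose the division comparison in place of the randomised one. Section 2.4.8 never ties the ANOVA to Aim 1 or to post-training scores, and it can be read as a description of two coaching populations. This stands. But if it is descriptive, Aim 1 has no stated inferential test of the training at all.
- **Who is trained.** The 47% to 53% dilution might be taken as a property of the plan. It is conditional, because the sections on who is trained disagree.
- **What is measured in June 2016.** Section 2.4.7.1 describes that form only as assessing retained knowledge. Whether perception and readiness are measured again is not stated, so the remedy may need more than new wording.
- **Modest ambition and few teams.** Aim 1 is framed as exploratory, and 19 teams give a wide interval. This lowers the severity. It does not make an uncontrolled contrast preferable to a randomised one that the planned questionnaires largely allow.

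The specified comparison of injury incidence between the study groups is unaffected.

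**Conclusion.** The point holds within the text available. Neither the objectives nor 2.4.8 states an analysis of coach scores that uses the randomisation, and the contrasts they do state cannot separate the training effect from retesting, turnover, outside courses or divisional differences. This is true whatever the division ANOVA was meant to do.

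The dilution to 47% to 53% applies only if training is confined to the intervention arm, coach numbers per team are equal, and the division contrast is read as a training effect. The better contrast is less biased but imprecise, at about 1.37 SD detectable with 80% power under one coach per team and no baseline adjustment.

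This should be fixed. Confidence is moderate, because of Appendix J and the conflict over who is trained.

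**What to change.** Subject to what Appendix J already contains:

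1. In 2.4.8 and in the Aim 1 objectives (1.3 and 2.4.1.1), state that the training effect is tested in second-division coaches by randomised arm. Use the June 2016 score adjusted for the preseason 2015 score, with team as the cluster or with team means, and report a confidence interval.
2. State a rule for coaches who have no baseline because they arrived after it. Confirm that the preseason 2015 form is completed before the training, which is dated differently in 2.4.6 and 2.4.7.1.
3. Confirm that the full Appendix K questionnaire, covering perception and readiness as well as knowledge, is used at both time points in both arms.
4. Keep the immediate post-training score as a within-arm description and the division ANOVA as a descriptive comparison with a stated time point.
5. Reconcile 2.2 and 2.4.4 with 2.4.6 and 2.4.7.1 on which coaches receive which training. This decides what the arm contrast measures, above all for first aid knowledge.

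The cost is mainly wording, because preseason and June 2016 questionnaires are already planned and are not limited to one arm. If the June 2016 form covers knowledge only, the remaining sections must be added. The price in inference is a wide interval from 9 versus 10 teams, which the plan should acknowledge.
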